## Abstract

**Background:**

This randomised controlled trial demonstrates the effectiveness of a value-based intervention program to encourage a physically more active lifestyle among physically inactive adults aged 30 to 50 years. The conceptual framework of the program is based on an innovative behavioural therapy called Acceptance and Commitment Therapy (ACT) that aims to increase an individual’s psychological flexibility and support behaviour change towards a higher quality and more meaningful life.

**Methods:**

Participants will be randomly allocated to a feedback group (FB) or an Acceptance and Commitment based (ACT + FB) group. Both the groups will receive written feedback about their objectively measured physical activity levels and offered an opportunity to attend a body composition analysis. In addition, the Acceptance and Commitment based group will attend six group sessions and be given a pedometer for self-monitoring of their daily physical activity throughout the 9-week intervention. The group sessions aim to clarify individual values and enhance committed actions towards the goal of achieving a more meaningful life. Participants will also be taught new skills to work on subjective barriers related to physical activity. Physical activity will be measured objectively by an accelerometer over seven consecutive days and by self-reported questionnaires at the baseline, as well as at 3, 6, 9 and 15 months after the baseline measures. In addition, psychological well-being will be measured through the questionnaires, which assess mindfulness skills, psychological flexibility, psychological distress and depressive symptoms.

**Discussion:**

This study’s objective is to demonstrate a research protocol for a randomized controlled study motivating a physically more active lifestyle based on one’s own values among physically inactive adults. The aim of the study is to evaluate the feasibility and intervention efficacy on physical activity and psychological well-being, and discuss challenges in motivating physically inactive adults towards physically more active lifestyles.

**Trial registration:**

ClinicalTrials.gov, number NCT01796990.

## Background

The promotion of physical activity is one of the major challenges for public health. Sedentary lifestyle has become a widespread health problem and it is one of the major causes of chronic diseases, like type II diabetes and cardiovascular disease [1]. By increasing physical activity especially among physically inactive individuals, their health could be substantially improved [2]. However, despite the fact that individuals are very well aware of the health benefits of physical activity, they are often unable to take action or change their behaviour and adopt a healthier lifestyle [3]. Only half of the physical activity intervention studies have been successful in increasing physical activity levels [4]. The poor effectiveness of physical activity interventions is partly due to insufficient information about the effective methods that work, especially among the physically inactive groups. In addition, there is a great need for methods to enhance individual motivation and challenge individuals to change their lifestyles in the long run in a cost-effective manner [5].

Acceptance and Commitment Therapy (ACT) is an innovative behavioural therapy approach based on functional contextualism [6]. The core analytic unit is the ongoing act in the context and the focus is on the whole event. ACT aims to increase psychological flexibility, which can be defined as the ability to be in the present moment with full awareness and openness to experiences and to take action guided by one’s values [6,7]. Instead of focusing on how one should act or behave according to the certain instructions or recommendations (e.g., for example related to a healthier lifestyle), the emphasis is on the behaviour that works in relation to value-based goals. Research evidence has shown that ACT-based approaches may help individuals to live in more flexible ways, and have more meaningful lives according to their own values, and has proven to be powerful in overcoming many kinds of mental and health-related problems [8]. In the area of health, the results have shown ACT to be successful in the treatment of numerous health conditions (e.g., chronic pain [9], type II diabetes [10], weight regain among bariatric surgery patients [11,12] and depression [13]) and associated with better psychological and quality of life scores [6].

The ACT approach can be divided into two parts. The first part includes acceptance and mindfulness processes, and the second part includes commitment and behavioural change processes. Acceptance refers to the process in which individuals can choose to experience the full range of private experiences, without having to change or defend against them. Mindfulness is a process that concentrates on the present moment as it is, not living excessively in the past or in the future. Commitment and behavioural change processes focus on value-based actions and behaviour, which lead towards a higher quality and more meaningful life. ACT has been delivered both in individual and group psychotherapy and coaching formats, and applied to a wide variety of clinical conditions and client groups [14].

In the context of physical activity promotion, only a few studies have shown that ACT could have potential in enhancing physical activity [15,16]. However, more research is needed to test the feasibility of this approach especially among the physically inactive ones. This paper will present the research protocol and methods used in the study, which aim to evaluate the effectiveness of the value-based approach in motivating physically more active lifestyles among physically inactive adults.

## Methods

### Study design

The design of the study is a randomized controlled trial (Figure 1). It will evaluate the effectiveness of physical activity and psychological well-being in the Acceptance and Commitment based (ACT + FB) group versus the feedback (FB) group only.

**Figure 1 F1:**
[figure not shown]
Flow diagram of the progress of the study.

The trial will be conducted in two phases: the first phase from autumn 2011 to December 2012, and the second phase from autumn 2012 to December 2013. The protocol was approved on 20.6.2011 by the Scientific Ethics Committee of the University of Jyväskylä, Finland. The trial is registered with ClinicalTrials.gov, number NCT01796990.

### Study population

The study population will consist of working adults aged 30 to 50 years who are physically inactive, defined as not meeting the current physical activity recommendations [1].

### Procedure for recruitment, randomization and allocation

Physically inactive adults will be recruited by advertisements in the local newspaper. All interested individuals will be screened in more detail by an online-questionnaire. The criteria for selection are: 1) age 30–50 years, 2) working status, and 3) not meeting the current physical activity recommendations [1]. The evaluation of the physical activity level will be determined by the questions: “During the last 7 days, on how many days did you carry out at least moderate intensity physical activity that lasted for at least 10 minutes each time and for a total of at least 30 minutes during one day?” The response options ranged from 0 to 7 days per week. Please include all activity for which the physical effort is moderate or harder including transportation to work and leisure time physical activity. This kind of activity accelerates the heart rate and breathing (e.g., brisk walking, running, and heavy gardening). In addition they were asked “How much time in total did you spend doing this type of physical activity during leisure time?” Estimate to the nearest half an hour [17].

All eligible participants will receive written confirmation of their acceptance into the study and be informed about the study protocol. The participants will give written informed consent if they agree to enroll in the study. Participants will be randomized into one of two parallel study groups, the Acceptance and Commitment-based group (ACT + FB) or feedback group (FB) only (see Figure 1).

### Interventions

#### Feedback group (FB)

The participants will get written feedback about their physical activity level after the baseline and after 3, 6, 9 and 15 months follow up. This individual written feedback includes information on participants’ objectively measured daily physical activity level compared to the current physical activity recommendations by using the histograms and graphs. Individual feedback will be posted home and will not include face to face interaction. As an incentive for participation, participants will also have opportunity to attend a body composition analyze and get short, personal interpretation and feedback of the results in the research center.

#### The Acceptance and Commitment-based Group (ACT + FB)

The Acceptance and Commitment-based group (ACT + FB) will be subject to the same procedures as the feedback group. In addition, they will participate in the ACT-based program and be given a pedometer for self-monitoring of their daily physical activity during the intervention program. The intervention program consists of six group sessions during the 9-week period of time, with each session lasting about 90 minutes (see Table 1). The sessions will be led by three to five group leaders, including the researcher. The group size is 8–10 participants per one group. All the group leaders will be trained in the ACT approach and supervised by the responsible researcher (AK). Participants will also get their own workbook, which will contain short descriptions of the sessions, and all individual reflections and notes.

**Table 1 T1:** Content of the six group sessions in the Acceptance and Commitment-based group

**Topics of the group sessions**	**Key points and aims of the sessions**
1. Health behaviour	What are the factors affecting my health behaviour/well-being? What is the direction I want to move in? What are the steps I have taken in order to try to change my well-being?
2. Values and important things in life	What are the most important values for me?
	Am I living or behaving according to my values?
3. Value-based actions and barriers	What are my specific goals and actions that support my valued behaviour?
	What kind of subjective barriers or explanations have I related to physical activity?
4. Living in the present moment and self-regulation skills	How do I contact the present moment?
	How do I use mindfulness skills in order to be more aware of my own behaviour in everyday life?
5. Self-processes and physical activity	How do I see myself and how does it affect my behaviour?
	Can I be more aware of the way I am thinking about myself and learn nonreactive ways to respond to these thoughts?
6. Flexible actions	How am I doing? What are the actions which help me to achieve my desired outcomes? Do I need to change my goals? Am I living according to my values?
	Can I be more flexible in my behaviour and physically active lifestyle?

The program aims to enhance physically active lifestyles and well-being through important life values and build committed action based on the chosen important values. The program will start with an analysis of health behaviour and reflections about values and important things in life. After value clarification, participants will make concrete action plans and define their own goals. The emphasis will be placed on small and feasible everyday actions, rather than demanding exercise goals. In order to achieve the set goals, participants are taught mindfulness skills and new ways to deal with the barriers. The purpose of learning mindfulness skills is to be more aware of one’s own thoughts, emotions and automatic behaviour patterns. By noticing these automatic thinking styles or routines, participants will have a better ability to consciously change their own behaviour in the everyday life context.

Every session includes mindfulness exercises, pair and group discussions and homework related to the topic of the session. The intention of homework is to encourage participants to also work with the topics between the sessions and transfer learnt skills into their own living context. The group leader’s role is to introduce the topics, teach new skills, lead the ongoing discussion and provide a context in which participants are willing to share their own experiences, thoughts and feelings. The program does not include psycho-educational elements, counseling on health, information about the health benefits of physical activity, or concrete physical exercise.

Table 1 Content of the six group sessions in the Acceptance and Commitment Therapy (ACT) intervention group.

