### Statistical analysis

Data will be analyzed using the Mplus statistical package 7.1 [32]. The intervention effect on primary and secondary outcome measures will be estimated and tested for significance. Analyses will be controlled for possible baseline differences between the ACT + FB and FB groups. Cohen’s *d* will be used to estimate the effect size of the intervention effect. An effect size of 0.2 is considered small, 0.5 is medium, and 0.8 is large [33]. Furthermore, differences in the stability of the outcome measures between the ACT + FB and FB groups will be examined using multiple-group modeling techniques. Full information maximum likelihood (FIML) estimation under the assumption of data missing at random (MAR) will be used in analyzing incomplete data. As the normality assumption is violated, maximum likelihood with robust standard errors (MLR) will be used. The significance level of the study will be set at 0.05.

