### Sample size

Power calculations were performed in order to determine the sufficient sample size to detect the significant intervention effect at a significance level of α = 0.05. Analysis was conducted for one of the primary outcome measures, objectively measured time spent in health-enhancing physical activity (HEPA time, min/day). A sample size of 100 (50 per group) would be sufficient to detect a medium-sized effect at the power level of 85%. In this case, a difference in a change in the HEPA time between the ACT + FB and FB groups equal to 5 minutes per day would be detected at appropriate levels of statistical power. Power calculations were based on Monte Carlo simulation studies and were performed by using the Mplus statistical package [32].

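### The described analysis and the 85% power make no provision for clustering by therapy group in the ACT + FB arm; if within-group correlation is positive, precision and power are overstated

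*Protocol article*

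**What the plan says.** The Interventions section describes two different modes of delivery. In the ACT + FB arm there are six sessions of about 90 minutes over nine weeks, held in groups: "The group size is 8–10 participants per one group". On staffing it says: "The sessions will be led by three to five group leaders, including the researcher". Interaction is part of the treatment: "Every session includes mindfulness exercises, pair and group discussions and homework related to the topic of the session". In the FB arm each participant is posted an individual report, with no face-to-face contact attached to it. Participants are randomised individually.

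The Statistical analysis section specifies Mplus, control for baseline differences, multiple-group modelling by trial arm, and full information maximum likelihood for missing data. On standard errors it says that "maximum likelihood with robust standard errors (MLR) will be used", and the reason given is violation of normality. It adds: "The significance level of the study will be set at 0.05".

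The Sample size section says: "A sample size of 100 (50 per group) would be sufficient to detect a medium-sized effect at the power level of 85"%. The basis is a Monte Carlo simulation whose model, variances and correlations are not given.

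Neither section mentions therapy group, leader, an ICC, a design effect, or a multilevel or cluster-robust option.

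**The concern.** People who discuss, practise and set goals together for nine weeks may end up more alike than people treated separately. Individual randomisation does not remove a correlation that arises after allocation. If it is positive, the mean of the ACT + FB arm varies more than 50 independent observations would suggest.

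Nothing the analysis section names deals with this. Robust standard errors chosen for non-normality do not correct for dependence between participants unless a cluster variable is specified. Full information maximum likelihood addresses missing data. The groups in the multiple-group modelling are the two trial arms.

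The standard error of the between-arm contrast is at stake, and with it the interval, the p-value and the claimed power. The primary and secondary outcomes all rest on this one comparison, though the ICC may differ between outcomes and between visits.

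**Working it through.** **Inputs from the protocol.** 50 per arm and 85% power (Sample size); alpha 0.05 (Statistical analysis; two-sided assumed, as sidedness is not stated); therapy-group size m = 8 to 10 (Interventions). Number of therapy groups if 50 are in the arm: 50/10 = 5 to 50/8 = 6.25.

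**Assumed input.** ICC from 0.01 to 0.10. The protocol gives no value.

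**1. The plan's own figure.** The Statistical analysis section sets the scale ("An effect size of 0.2 is considered small, 0.5 is medium, and 0.8 is large"), so a medium effect is d = 0.5. Under independence, power = Φ(0.5/√(2/50) − 1.96) = Φ(2.5 − 1.96) = 70.5%, or 80.4% one-sided. The stated 85% needs d = (1.96 + 1.036) × √(2/50) = 0.599, or d = 0.5 with baseline adjustment at a correlation of about 0.55. Neither is stated. This does not show that 85% is wrong, because the simulation model is not given. Below, 85% is accepted as correct under independence, which is equivalent to d = 0.599.

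**2. Design effect in one arm.** In SD units:
- DE = 1 + (m − 1) × ICC, in the ACT + FB arm only
- Var(difference) = (DE + 1)/50, against 2/50 under independence
- true SE / naive SE = √((DE + 1)/2)
- type I error of the naive test = 2 × (1 − Φ(1.96/SE ratio))
- power allowing for clustering = Φ(0.599/√((DE + 1)/50) − 1.96)

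Example with m = 9 and ICC = 0.05: DE = 1.40; SE ratio = √1.20 = 1.095; type I error = 2 × (1 − Φ(1.789)) = 7.4%; power = Φ(0.599/0.2191 − 1.96) = 78.1%.

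| ICC | DE (m = 8 to 10) | SE ratio | Type I error, groups ignored | Power, large-sample | n per arm for 85% |
|---|---|---|---|---|---|
| 0.01 | 1.07-1.09 | 1.02 | 5.4-5.5% | 83-84% | 52-53 |
| 0.05 | 1.35-1.45 | 1.08-1.11 | 7.1-7.7% | 77-79% | 59-62 |
| 0.10 | 1.70-1.90 | 1.16-1.20 | 9.2-10.4% | 70-73% | 68-73 |

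**3. Simulation check of type I error.** Five groups of 10 against 50 independent controls, with a t-test ignoring therapy group, gave 5.4%, 6.1%, 7.6% and 10.2% at ICC 0.01, 0.02, 0.05 and 0.10. This agrees with the formula.

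**4. Small-sample power.** With only five groups, the large-sample column is optimistic. A conservative alternative compares the five ACT group means with the 50 FB participants, using Satterthwaite degrees of freedom. Simulated power was about 79% at ICC 0, 69% at 0.05 and 61% at 0.10.

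**The case against.** **The article does not say that participants are treated as independent.** A reader might infer this from the model described, but the text does not state it. The article condenses a fuller protocol, the software named could take a cluster variable, and the detailed random-effects structure commonly sits in a statistical analysis plan. This stands, and it limits the point to what is written: a specific estimator with a reason that is not clustering, and a fixed power figure, neither with a stated allowance for therapy group.

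**The effect is conditional.** A reader might conclude that the standard errors are too small and that type I error exceeds 5%. Both need a positive ICC, which the protocol does not give. At 0.01 the inflation is negligible.

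**The null hypothesis matters.** If the programme affects nobody, grouping after individual randomisation cannot change outcomes, and a test ignoring groups keeps about 5%. The inflation applies where therapy groups truly differ but the average effect is zero. This stands. The variance of an estimated non-zero effect, and so its interval, remains understated whenever the correlation is positive.

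**Leader effects cannot be sized.** One fixed leader per therapy group is a tempting reading, but the article gives only a total of three to five leaders and does not say how they are assigned. Nor does it say that group membership is recorded.

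**The remedy has a price.** With five or six groups, small-sample methods cost power even at an ICC of zero (about 79% instead of 85% in the group-mean test). This is a real trade-off.

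**Conclusion.** The concern holds in conditional form and should be fixed. The design is partially nested on the protocol's own description, and neither the described analysis nor the power statement provides for it.

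The size depends on the ICC: close to nothing at 0.01, and material at 0.05 to 0.10. There, a nominal 5% test of a zero average effect runs at about 7 to 10%, and the true standard error is 8 to 20% above the naive one. The claimed 85% power becomes 77-79% at 0.05 and 70-73% at 0.10 by design effect, and about 69% and 61% under the conservative small-sample test.

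These figures assume 50 per arm, therapy groups of 8 to 10, a two-sided test, and 85% being right under independence. Whether 85% can be reproduced at all is a separate question on which this point does not depend.

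**What to change.** 1. Record therapy group and leader for every ACT + FB participant.
2. Analyse the primary contrast as partially nested: a random therapy-group effect in the ACT + FB arm only (each FB participant a cluster of one), separate residual variances by arm, and small-sample degrees of freedom (Satterthwaite or Kenward-Roger). With five or six groups, a plain cluster sandwich estimator is not a reliable substitute.
3. Report the estimated ICC.
4. Rerun the Monte Carlo power simulation with the therapy-group term and restate power as a range over ICC 0.01 to 0.10, leaving the sample size as it is. If the full protocol or analysis plan already contains such a term, say so and quote the ICC used.

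The cost is one extra variable or two in the data set, some analysis code and a sentence in the plan. The downside is wider intervals and a less favourable stated power.

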### Outcome measures

Measurements will take place at baseline and 3, 6, 9, and 15 months after the baseline (Figure 1). The baseline demographic characteristics of participants will also be recorded. The primary outcome measures will be based on physical activity.

### Primary outcome measures

#### Objectively measured physical activity

Physical activity will be measured objectively by an accelerometer (Actigraph GT1M, GT3X, Actigraph, Pensacola, Florida). The ActiGraph accelerometer is a small and light instrument that records integrated acceleration information as an activity count, providing an objective estimate of the intensity of vertical bodily movement. Participants are instructed to wear the accelerometer on their right hip, attached by an elastic belt during all waking hours for seven consecutive days [18]. Outcome variables were: sedentary time (< 100 counts per minute, cpm), time spent on light intensity physical activity (LPA time, min/day, 100–759 cpm), time spent on lifestyle physical activity (LIFEPA, min/day, 760–1951 cpm), time spent on moderate-to-vigorous intensity physical activity (MVPA time, min/day, 1952 ≥ cpm), time spent on health-enhancing physical activity (HEPA time, min/day) and steps per day [19]. HEPA was defined as continuous MVPA lasting at least 10 minutes at a time according to the current physical activity recommendation [1]. The validity and reliability of the Actigraph GTX3 has been shown to be similar to the GT1M devices in laboratory testing and for the measurement of everyday activities [20,21]. The ActiLife accelerometer software (ActiLife version 5) was used for data collection, and customised software was used for data reduction and analysis. In order to meet at least 80% of the data reliability criterion [18], at least three days of the seven days and for a minimum of 500 minutes per day is set as a minimum criterion for the representative data.

